### Data sources & collection

Dead cases (A) and matching diseased controls (E) will be extracted by KIT London, and matching general population controls will be retrieved by the HSCIS at Exeter. Recently diagnosed cases will be extracted by KIT London, and matching general population controls will be retrieved by the HSCIS at Exeter. Tumour pathology variables will be obtained from the National Cancer Data Repository (NCDR) via KIT London, but may only be available for certain regions (i.e. previous cancer registries). Breast screening data will be obtained, as for cervical and bowel screening variables, from the HSCIS. Bowel screening variables will not be sought for the pilot phase.

The data will be checked and cleaned by the PRU Senior Data Manager, transferred to separate Oracle tables, and stored on a UNIX server kept in a secure server room within the Wolfson Institute of Preventive Medicine. Access to the Oracle database is from PCs on the secure QMCR network using SQLNET.

All data will be processed in accordance with NHS Information Governance guidelines.

### Variables

A list of all the variables to be retrieved during the ongoing evaluation study is presented in Table 1.

**Table 1 T1:** Variables of interest

**Patient characteristics**	**Primary breast tumour attributes**	**Screening data**
	**(all primary breast tumours)**	
Patient unique ID	Tumour unique ID	NHS registration by age 47
NHS number	Tumour status (in situ or invasive)	Screening office/centre
Gender	ICD10 code	Episode date
Case or Control	Date of tumour diagnosis	Screen / Test date
Date of birth	Tumour detection mode	Screen / Test outcome
Patient status (alive or dead at end of study period)	Treatment	
Cause of death – Breast cancer (where applicable)	Tumour size	
Date of death (where applicable)	Number of lymph nodes	
Age at death (where applicable)	Stage	
Date of tumour diagnosis / pseudo-diagnosis	Grade	
Age at tumour diagnosis / pseudo-diagnosis		
Cancer registry		
Geographical area		
IMD (Postcode-based)		

Information retrieved regarding living area on which to match cases and controls will vary depending on the study (pilot or main phase) and time of evaluation. NHAIS information will be obtained from HSCIC for Health for all cases and controls used for CC-1, CC-3a/b and CC-4 studies, while CN information will be used by KIT London to match cases and controls for CC-2.

### Study size / Power calculation

The main phase of the study will cover the whole of England with biennial accrual of potentially thousands of cases (circa 18,000 (CRUK, Accessed 28 March 2013 [1])), for which statistical power will not be an issue for any of the case studies, and for which there will be considerable precision. The large sample size will also allow subset evaluation, notably by time since last screen. The sample size for the pilot study was estimated to enable sufficient power to answer the primary objectives addressed by CC1 and CC2 with relative confidence. Results of the pilot with respect to CC3a, CC3b and CC4 objectives will provide the prior estimates currently lacking to perform power calculations.

**CC1.** For the matched comparison of the breast cancer dead cases (A) with the general population controls (B), assuming an odds ratio of 0.7 for the event of ever attending screening (Broeders et al., 2012 [11]), around 900 dead cases and 1800 living controls would confer 90% power to detect such an effect size at the 5% significance level when using a 2-sided test (Machin et al., 1997 [12]).

**CC2.** For the matched comparison of the breast cancer dead cases (A) with the diseased controls (E), no estimate of the odds ratio is available, but it can be assumed to be 0.70 or less for the event of ever attending screening, to be at least consistent with CC1. With only one control per case, 1200 / 900 dead cases and the same number of controls will be required to obtain 90% and 80% power, respectively.

Missing data for some of the breast tumour attributes and treatment can be close to 40-50%, and the pilot sample size will be inflated accordingly. Sensitivity analyses will be conducted for various possible scenarios of non-random missing status.

We are therefore planning to collect pilot data from at least 1400 dead cases (A), together with 2800 general population controls (B) and 1400 diseased controls (E) matched for these. We will also collect at least 1400 recently diagnosed cases (C) and 2800 general population matched controls (D). There will be some degree of overlap between populations (A, C), (C, E) and (B, D).

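### The pilot target of 1400 CC2 pairs is presented as inflated for 40-50% missing tumour and treatment data, but it is not that inflation of the plan's own 900 or 1200 pairs

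*Protocol article*

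**What the plan says.** All the figures are in the protocol article, under Study size / Power calculation.

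- CC1: at an odds ratio of 0.7 for ever attending screening, "around 900 dead cases and 1800 living controls would confer 90% power" at the two-sided 5% level.
- CC2: no odds ratio is available, but "it can be assumed to be 0.70 or less for the event of ever attending screening". For this 1:1 design the stated need is: "1200 / 900 dead cases and the same number of controls will be required to obtain 90% and 80% power, respectively".
- Incomplete variables: "Missing data for some of the breast tumour attributes and treatment can be close to 40-50" per cent. The section then promises an allowance for this: "the pilot sample size will be inflated accordingly".
- Result: "We are therefore planning to collect pilot data from at least 1400 dead cases (A"), alongside 2800 population controls and 1400 diseased controls.

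The same section says that the pilot was sized for the primary objectives of CC1 and CC2. Under Statistical methods, the CC2 primary objective covers the effects of both screening attendance and cancer treatment on prognosis. The CC2 regression is adjusted for stage and other pathological features, and all analyses use conditional logistic regression.

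**The concern.** The section gives a requirement, a rate of missing data and a promise to inflate, and then a total introduced as the consequence. The total is smaller than any correct inflation of either requirement. The incomplete variables are the ones the CC2 primary objective needs: treatment is one of the two exposures of interest, and tumour attributes are the adjustment set.

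CC2 is one of only two studies the pilot is sized for. A reader would take from the text that the adjusted CC2 analysis keeps 80% or 90% power after 40-50% of the tumour and treatment data are lost. On the plan's own figures it does not, if incomplete pairs drop out.

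**Working it through.** **Inputs stated in the sample size section.** CC2 odds ratio 0.70, one control per case, 1200 pairs for 90% power, 900 for 80%, missing data 40-50%, planned pairs 1400. The two-sided 5% level is stated for CC1 and is assumed here to apply to CC2.

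**Step 1. Reproduce the base sizes.** Attendance among controls, p0, is not given in this section. With odds ratio 0.7, attendance in cases is p1 = 0.7·p0 / (1 − p0 + 0.7·p0). The usual two-proportion formula without continuity correction gives:

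| Assumed p0 | p1 | CC1 cases, 1:2, 90% | CC2 pairs, 90% | CC2 pairs, 80% |
|---|---|---|---|---|
| 0.77 | 0.701 | 637 | 855 | 639 |
| 0.86 | 0.811 | 904 | 1216 | 909 |
| Plan | not stated | 900 | 1200 | 900 |

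An attendance of about 86% reproduces all three stated sizes. With continuity correction, 85% does so about equally well (886, 1192 and 900). The 900 and 1200 are therefore coherent with each other and are taken as given. Steps 2 to 4 do not depend on p0.

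**Step 2. Inflate as promised.** Required pairs = n / (1 − d), where d is the fraction of pairs lost.

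| Target | d = 0.40 | d = 0.50 |
|---|---|---|
| 80% power, n = 900 | 900/0.60 = 1500 | 900/0.50 = 1800 |
| 90% power, n = 1200 | 1200/0.60 = 2000 | 1200/0.50 = 2400 |

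The common mistaken form n × (1 + d) gives 1260 and 1350 for 900, and 1680 and 1800 for 1200. None of the eight figures is 1400.

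**Step 3. Work back from 1400.** 1400 × 0.60 = 840 and 1400 × 0.50 = 700 complete pairs. Both are below 900.

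**Step 4. Loss that 1400 can absorb.** For 80% power, 1 − 900/1400 = 35.7%. For 90% power, 1 − 1200/1400 = 14.3%. Neither reaches the bottom of the stated 40-50% range.

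**Step 5. From women to pairs.** In a complete-data conditional logistic fit with one control per case, a gap in either woman removes the pair. If 40-50% is a rate per woman, the pair loss is at least that large when cases and controls have the same rate, and larger unless the gaps fall in the same pairs.

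**Step 6. Power at 840 and 700 complete pairs (illustrative).** Same formula, odds ratio 0.7:

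| Assumed p0 | 840 pairs | 700 pairs |
|---|---|---|
| 0.86 (reproduces 900/1200) | about 77% | about 69% |
| 0.77 | about 90% | about 84% |

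The 77% is the national coverage at ages 53-70 quoted under Self-selection bias. It is not ever-attendance, and it does not reproduce the plan's sizes. These power figures treat the comparison as attendance alone in the complete pairs and make no allowance for precision lost through covariate adjustment.

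**The case against.** The strongest reply is that 900 and 1200 were derived for ever attending screening, which comes from screening records and not from tumour or treatment fields. An attendance-only CC2 comparison keeps all 1400 pairs, more than the 1200 required for 90% power. This stands, and it limits the point to the adjusted analysis. It does not remove the error: the section itself ties the inflation to the tumour and treatment variables, and the CC2 primary objective and regression use them.

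Other replies also stand in part:

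- The 40-50% applies to some variables and is worded as what can occur, and 1400 is a floor. Actual loss may be smaller. But 40-50% is the plan's own basis for inflating, and the floor is what it says results.
- At 40% pair loss and the 80% target, the gap is only 60 pairs (840 against 900). At 50%, or against the 90% target, it is large.
- The protocol article does not specify complete-case deletion, and handling of missing covariates may be set out in an analysis plan that is not shown. The shortfall is therefore conditional on complete-pair analysis. The planned sensitivity analyses for non-random missingness address bias, not the number of usable pairs.
- The odds ratio is assumed to be 0.70 or less. At 0.65 and 86% attendance, 840 and 700 pairs give about 91% and 85% power. The stated sizes, however, reproduce at 0.70.

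A reader might infer that the pilot's true CC2 power is 69-77%, or 41-55% if data are missing independently in the two women (1400 × 0.36 = 504 or 1400 × 0.25 = 350 pairs). The document does not support either as a fact. Both ranges rest on a back-solved attendance of 86% and on complete-pair deletion. The lower one also needs independence within pairs matched on Cancer Network and on close diagnosis dates, where shared gaps are plausible.

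**Conclusion.** The concern holds in limited form. The figure of 1400 CC2 pairs is not an inflation of 900 or 1200 for 40-50% missing data, whatever attendance is assumed. The correct figures are 1500-1800 and 2000-2400. For a complete-pair analysis of the adjusted CC2 model, 1400 falls short of even the 80% requirement by 60 pairs at 40% loss and 200 at 50%.

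How much power is lost cannot be fixed from the document, because it depends on the unstated attendance and on how incomplete pairs are handled. The attendance-only CC2 comparison is unaffected, as is CC1, which needs 900 cases and no tumour data.

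This should be fixed, but it does not undermine the study. It concerns a pilot, the main phase expects about 18,000 cases (with CC2 limited to regions that have the data), and the document ties no decision rule to a null CC2 pilot result.

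**What to change.** Amend the sample size text as follows.

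1. Remove the statement that 1400 is inflated for 40-50% missing data.
2. State that 1400 pairs meet the 90% target for the unadjusted attendance contrast only. For the adjusted CC2 analysis they meet 80% power only if no more than about 36% of pairs are incomplete, and 90% only if no more than about 14% are.
3. State the control attendance assumed, and give adjusted-analysis power at 840 and 700 complete pairs on that assumption. The figures in the working are illustrations, not values to adopt.

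Alternatively, raise the CC2 target to n / (1 − d). Multiple imputation, to keep incomplete pairs, is an option alongside the planned sensitivity analyses. It is not required, recovers only part of the information, and in its standard form assumes data missing at random.

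The textual change costs a less favourable power statement and no extra cases. Raising the target would mean at least 100 more pairs (1500 − 1400) and up to 1000 more (2400 − 1400), on pair-level loss.

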### Bias & Effect modification

The case–control design is potentially prone to a number of biases (Walter, 2003 [5]), in particular some that could confer a bias *in favour of screening*, and which are addressed either at the design stage by choosing appropriate selection criteria, or at the analysis stage by using suitable statistical methods.

#### **
*Ascertainment bias*
**

Among the screen-detected cases who die with primary breast cancer as a contributing cause on their death certificate (including DCO cases), there are those who would have died without any diagnosis of breast cancer, had they not been screened, forming part of overdiagnosis due to screening (Duffy, 2010 [13]). This introduces a bias *against screening* when assessing the impact of screening attendance on mortality, although unlikely to be a large one. It will be addressed at the analysis stage by a series of sensitivity analyses, assuming a range of plausible magnitudes of the bias. This bias may also qualify interpretation of the results from an analysis assessing the impact of time since last screen on the case–control status among screen-detected cancer patients.

In contrast, women with multiple co-morbidities who may be less likely to have breast cancer recorded as cause of death may be less likely to be screened. Consequent exclusion of those women from our datasets would confer a bias *against screening*.

#### **
*Exposure (screening) opportunity bias*
**

Once diagnosed with breast cancer, the cases come under clinical management and do not continue with routine breast screening as before. The controls, however, may continue to attend screening up to the time of the case being entered into the study. This potential bias is addressed at the design stage by giving the controls a pseudo-diagnosis date that is the same as that of their matched case and screening history is only considered up to that date (Connor et al., 2000 [14]). This is in fact an over-correction and results in a bias *against screening*. The fact of the case having necessarily a diagnosis of breast cancer and a control usually not having such a diagnosis, induces an artificially higher retrospective probability of screening exposure in the cases, a bias *against screening* (i.e. the screen-detected cases will always have this screen recorded at diagnosis, whereas the large majority of controls will not at pseudo-diagnosis). Simply excluding the detection screens from the histories would bias the results *in favour of screening*. When assessing the effect of ever having been screened, the major driver of this bias is prevalence screening, and for a mature programme with approximately 6 incidence screens for each prevalence screen, this bias is likely to be small. However, this bias may remain when using other measure of screening exposure. The extent of screening opportunity bias will be investigated by applying an analytical correction to the odds ratio using the method by Duffy et al., 2008a [15], and by performing sensitivity analyses in which the date of pseudo-diagnosis for controls will be extended by up to 4 years, the estimated average sojourn time for each screen-detected case, to counteract the artificially higher retrospective probability of screening exposure in cases (Connor et al., 2000 [14]).

But the major sources of bias in case–control studies are potential self-selection and lead-time biases (Puliti et al., 2011 [16]). Length bias will also be discussed. Note that lead-time and length biases will only affect analyses assessing the effect of screening on survival among cases (i.e. case-study 2), but not those assessing its impact on population outcomes (incidence or mortality).

#### **
*Self-selection bias (or non-compliance bias)*
**

Women who accept the invitation to screening (attenders) may have an a priori better health status (and a lower underlying risk of dying from breast cancer) compared with women who do not (non-attenders), and therefore are less likely to die from the disease. We would anticipate that this will confer a bias *in favour of* screening. Although this bias in favour of screening is unavoidable at the design stage, it can be approximately corrected for in the statistical analysis. In women diagnosed with breast cancer aged 47–52 (and their controls) we will look at two factors: “(invited and) screened”, “invited but not screened” compared to “not invited”. The odds ratio in “invited but not screened” can be used to adjust for the self-selection bias using the method by Duffy et al. (2002) [6]. This method cannot be used in older women as they will all have been invited.

The method developed by Duffy et al. (2002) [6] will also be used to correct the estimated odds ratio using data on participation in the NHSCSP (cervical) and/or NHSBCSP (bowel) screening programmes, rather than data on participation from the RCTs of mammographic screening. In the absence of self-selection, the relative risk of primary breast cancer (death/incidence) associated with breast screening for non-attenders at cervical or bowel screening would be expected to be equal to the relative risk in cervical or bowel screening attenders (after adjusting for breast cancer screening). In practice, the relative risk of primary breast cancer has been shown to be about 10% lower in non-attenders to RCTs (Duffy et al., 2002 [6]). The crucial element in correcting for self-selection bias is the risk ratio (termed “Dr”) for non-attenders versus attenders to cervical or bowel screening. This will be calculated for women who attended breast screening at least once and for women who did not attend a single screen, to control for attendance at breast screening. A range of denominator values for “Dr” will be assessed for sensitivity. One could compare primary breast cancer rates (i) in women who have had bowel/cervical screening - but not breast screening -with women who have had neither bowel/cervical nor breast screening; and (ii) in women who have had *both* bowel/cervical and breast screening with women who have only had breast screening. Data for women with age at diagnosis/ pseudo-diagnosis between 47 and 64 year-old who would have been invited to both the breast and cervical screening programmes will be used. Alternatively, data for women with age at diagnosis/pseudo-diagnosis between 60 and 69 year-old who would have been invited to both the breast and bowel screening programmes will be used. Also, in women under age 50, one could compare primary breast cancer rates in women who have, or have not had, cervical screening, hence by-passing the positive confounding between uptake of the various screening programmes.

Breast screening coverage of women aged 53–70 in England was 77% at 31st March 2012 (The HSCIC Breast Screening Programme – England report, 2011-2012 [17]).

In addition, self-selection will be addressed at an individual woman level by adjusting the regression model for participation in the other screening programmes, with careful adjustment for the confounding between attendances in different programmes: participation will be recorded as “Currently screened”, “Formerly screened” and “Never screened”, enabling all women to be included in the analysis.

For the pilot phase, a single self-selection factor will be estimated as the data covers one Strategic Health Authority (SHA) only (London); for the national phase, regional factors may be estimated to assess variation in self-selection between regions. This approach will be compared with adjusting the regression model for potential confounders, such as history of cervical/bowel screening, and socioeconomic (SEC) status. The Index of Multiple Deprivation (IMD) is an area-based measure of relative deprivation, derived from the womens’ postcodes based on census statistics for overcrowded housing and other factors, and is believed to be the main confounding factor relating to both the exposure (i.e. the decision to attend screening), and the outcome.

#### **
*Lead-time bias*
**

Lead-time is the amount of time by which the date of diagnosis has been advanced by screening detection as opposed to symptomatic occurrence. This confers a bias *in favour of screening*, which will be addressed at the analysis stage of case study 2 using two approaches: (1) “postponement of screen-detected cases” where the date of diagnosis for the screen-detected cases will be shifted forward for a period corresponding to the estimated lead-time (Gabe et al., 2007 [18]), and (2) statistical adjustment where the cases’ (and diseased controls, where applicable) additional follow-up time (between date of diagnosis and date of death/censor date) - observed purely as a result of lead-time - will be estimated by assuming an exponential distribution of the sojourn time, the period during which the tumour is asymptomatic but screen-detectable (Duffy et al., 2008b [19]). The estimates for mean sojourn time will be taken from Tabar et al. (2000 [20]).

Applying a restriction on the date of diagnosis during the selection of dead cases can also introduce a form of lead-time bias. Among cases who died from breast cancer on the same date, the screen-detected ones would have received their diagnosis earlier than the symptomatically-diagnosed cases, and therefore would tend to be excluded during the selection, introducing a bias in *favour of screening*. No restriction on the case’s date of diagnosis will be applied at the design stage, i.e. all women diagnosed after the inception of the NHSBSP, i.e. since 1990, will be included in the study.

#### **
*Length bias*
**

Length-biased sampling occurs when the chance of an observation being in a sample is proportional to a particular characteristic of the observation. In the context of screening, length bias is the phenomenon whereby slower-growing, less aggressive tumours (including DCIS) have a longer pre-clinical screen-detectable period (PCDP) and are therefore more likely to be screen-detected compared to faster-growing, more aggressive cancers. This will confer a bias *in favour of screening*, which will be addressed at the analysis stage of case-study 2 by performing sensitivity analyses. Two latent tumour populations will be assumed, one – the “length bias group” - with both a higher probability of being screen-detected and a correspondingly lower probability of fatality, whether actually detected by screening or symptomatic (Duffy et al., 2008b [19]).

The extreme form of length bias is overdiagnosis, defined as the diagnosis of cancers which would not have come to clinical attention in the patient’s lifetime had screening not taken place. Overdiagnosis can be estimated by comparing cumulative incidence in screened and unscreened populations several years after screening stops (Biesheuvel et al., 2007 [21]). Estimates of overdiagnosis obtained from observational studies vary widely according to the design used, i.e. dynamic populations or cohort populations (Puliti et al., 2011 [16]). In case–control studies, which are nested within a cohort population, overdiagnosis can be robustly estimated provided that (1) the difference in underlying risk of primary breast cancer between screened and unscreened populations (i.e. self-selection bias), and (2) the period of time by which the diagnosis is brought forward by screening (i.e. lead-time bias) are both accounted for (Duffy et al., 2010 [13], Puliti et al, 2011 [16]). In the absence of overdiagnosis, the initial increase in primary breast cancer occurrence in the screened group would be fully compensated by a similar decrease in cancers among older age groups no longer offered screening (“compensatory drop method”, Puliti et al., 2011 [16]).

In addition to investigating the extent of the different biases when examining the relationship between screening and mortality or incidence, identifying homogeneous strata that may (positively or negatively) modify the effect of the screening exposure on the outcome (effect modifiers), such as age at diagnosis / pseudo-diagnosis (5-year band), epoch of diagnosis (5-year band), and tumour detection mode of the cases will be of interest.

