### Participants: selection of cases & controls

#### **
*CC1 & CC2*
**

*Population of dead cases (A)* All women who died of primary breast cancer (as stated in part 1 of the death certificate) age 47–89, within the specified 2-year study period will be selected. Cases of women with only in situ primary breast cancer records (i.e. no invasive record) will be included, but Death Certificate Only (DCO) cases will be excluded. Case A women will have had their date of first diagnosis of primary breast cancer (in situ or invasive) age 47–89 and since 1990, and for subsequent phases of this evaluation (main phase onwards), they will not have been included as cases in previous evaluation periods, although they may have been included as controls, and may also be selected as a case C in the same evaluation.

*Population of cases A-matched general population controls (B)* For each case A, two women will be selected among the general population in the Health & Social Care Information Centre (HSCIC) database at Exeter who, are registered in the same National Health Applications and Infrastructure Services (NHAIS) system as the case at the case’s date of first diagnosis, are alive at the case’s date of death, and were born within 1 month either side of the case’s date of birth. Control B women may have had primary breast cancer (in situ or invasive) at the case’s date of first diagnosis. For subsequent phases of this evaluation (main phase onwards), they will not have been included as population controls B, E, or D in previous evaluation periods, although they may be included as a controls E or D within the same evaluation period.

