*Population of cases C-matched general population controls (D)* For each case C, two women will be selected from the general population in the HSCIC database at Exeter who, are registered in the same NHAIS system as the case at the case’s date of index diagnosis, are alive at case’s date of index diagnosis, and were born within 1 month either side of the case’s date of birth. For subsequent phases of this evaluation (main phase onwards), they will not have been included as population controls B, E, or D in previous evaluation periods, although they may be included as controls B or E within the same evaluation period.

Incident cases (C) and matched general population controls (D) will be selected *a posteriori* by the PRU, using tumour information, to suit the purpose of each case-study (see Figure 1).

**For CC3a**, incident cases (C) will be restricted to those women with invasive breast cancer, and matched general population controls (D) will be restricted to those women who have never had invasive primary breast cancer, but may have had in situ primary breast cancer prior to *and including* the case’s date of index diagnosis.

**For CC3b**, all incident cases (C) will be selected. For in situ cases, matched general population controls (D) will be restricted to those women who never had primary breast cancer (in situ or invasive) prior to *and including* the case’s date of index diagnosis; for invasive cases, to those women who never had invasive primary breast cancer, but may have had in situ primary breast cancer.

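### In CC1 the pseudo-diagnosis extension of up to 4 years has no stop at the matched case's death, so the sensitivity odds ratio can count control screens that came after it

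*Protocol article*

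**What the plan says.** In the protocol article, under Bias & Effect modification (Exposure (screening) opportunity bias), each control takes her matched case's diagnosis date as a pseudo-diagnosis date, and "screening history is only considered up to that date". The article accepts that this over-corrects and works against screening. It therefore plans two checks: an analytical correction to the odds ratio, and sensitivity analyses in which "the date of pseudo-diagnosis for controls will be extended by up to 4 years". The length is described as "the estimated average sojourn time for each screen-detected case" and the aim as "to counteract the artificially higher retrospective probability of screening exposure in cases".

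Under Participants: selection of cases & controls, CC1 cases (A) enter the study by dying of breast cancer in the study period. Their general population controls (B) must be women who "are alive at the case’s date of death, and were born within 1 month either side of the case’s date of birth". Freedom from breast cancer is not required of them: "Control B women may have had primary breast cancer (in situ or invasive) at the case’s date of first diagnosis".

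The article gives no rule for where the extended window ends if the case died before the extension ran out.

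**The concern.** The extension is a counterfactual device. A screen-detected case has her diagnosis brought forward and so loses later opportunities to be screened. Moving the control's date forward is meant to put the two women back on an equal footing. This works only while the extension does not exceed the time the case could have remained undiagnosed. In CC1 her death from the disease sets an absolute limit on that time.

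Past that limit, controls gain screening opportunity that the case could not have had under any scenario. The same section treats as a bias the fact that controls can go on being screened until the case enters the study. In CC1, entry is the case's death. For a case who dies within the extension, the sensitivity analysis therefore gives her controls more opportunity than the uncorrected comparison that the section sets out to repair.

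Extra screens in controls lower the odds ratio, that is, in favour of screening. An analysis meant to show how far opportunity bias could move the result would carry some opportunity bias of its own.

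**Working it through.** The article has no figure of its own to reproduce here: the 4 years comes from a cited source, and survival of fatal cases is not given. The check compares dates and then illustrates the size under stated assumptions.

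**Dates.** Set the case's first diagnosis at year 0, her death at year T and the extension at e years. The control's window runs to year e.
- If T ≥ e, the whole window lies before the case's death, control B is known to be alive throughout, and there is no problem.
- If T < e, the last e − T years of the window fall after the case's death. With T = 2 and e = 4, that is 2 of the 4 years.

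**Inputs.**
- e = 4 years, the stated maximum. A 2-year extension is shown for comparison.
- T exponential with mean m = 5, 8 or 10 years. This is an assumption, not a figure from the article.

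**Formulas.**
- Share of cases who die within the extension: P(T < e) = 1 − exp(−e/m).
- Mean share of the window lying after death: [e − m(1 − exp(−e/m))]/e.

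**Results for e = 4.**
- m = 5: 1 − exp(−0.8) = 0.55; (4 − 5 × 0.551)/4 = 0.31.
- m = 8: 1 − exp(−0.5) = 0.39; (4 − 8 × 0.393)/4 = 0.21.
- m = 10: 1 − exp(−0.4) = 0.33; (4 − 10 × 0.330)/4 = 0.18.

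**Results for e = 2.**
- m = 5: 1 − exp(−0.4) = 0.33; (2 − 5 × 0.330)/2 = 0.18.
- m = 10: 1 − exp(−0.2) = 0.18; (2 − 10 × 0.181)/2 = 0.09.

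**Wider range.** With medians instead of means, P(T < 4) = 1 − exp(−ln 2 × 4/median). This is 75% at a median of 2 years, 50% at 4, 37% at 6 and 24% at 10.

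**Upper bound in screens.** At m = 5 and e = 4, the time after death averages 4 × 0.31 ≈ 1.25 years. With 3-yearly screening and the 77% coverage quoted for ages 53–70, that is 1.25/3 × 0.77 ≈ 0.3 screens per extended control. This is a worst case: the shortest of the three mean survivals, the full extension, and every control of invited age. Diagnosis ages in CC1 run to 89 and the article puts the end of screening at 70, so the true figure is lower.

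**Which sets are extended.** The rationale refers to screen-detected cases, but the operation is stated for controls in general. A set whose case presented with symptoms has no screening lead time to offset, so extending its controls would only add opportunity.

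**The case against.** The strongest reply is that this is one clause about a supporting analysis in a condensed article. Truncation rules may sit in the full protocol or analysis plan, and nothing says that screens after the case's death will be counted. Four years is a maximum and is compatible with shorter, case-specific shifts. The mention of screen-detected cases may already imply the restriction. Adding exposure to controls is the declared purpose, because the main analysis is acknowledged to lean against screening, and an analytical correction runs beside it. The primary measure is ever having attended, and a further screen in a woman already screened does not change it.

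Most of this stands, and it limits the size of the point. It does not remove it. The article itself fixes the operation, its length and its rationale, and the rationale fails for any case who survived less than the extension. The effect will show mainly in the secondary measures, such as number of screens and time since last screen, for which the section itself warns that opportunity bias may remain.

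A reader might infer more than the text supports:
- **Controls B drop out by developing breast cancer.** They do not; the selection rules allow it.
- **Controls who die in the window gain exposure.** A dead woman has no further screens, so her death lowers exposure.
- **CC3a, CC3b and CC4 are seriously biased.** Controls D are checked only at the index date (they "are alive at case’s date of index diagnosis, and were born within 1 month either side"), so a control's own detection screen could be counted. Over 4 years, however, only about 0.5% would be diagnosed with invasive cancer at the article's all-age rate (1 − exp(−4 × 125.7/100,000)), and 1.0% to 1.4% at assumed rates of 250 to 350 per 100,000. Not all of these would be screen-detected.

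**Conclusion.** The point holds for CC1 and for this sensitivity analysis only. Read as written, the extension can run past the death of the matched case, and the resulting odds ratio then leans in favour of screening. Under assumed exponential survival with mean 5 to 10 years, a full 4-year extension would pass the death of 55% to 33% of fatal cases, and 31% to 18% of the window would lie after death. Both shares fall with shorter extensions, and time after death matters little for women outside screening ages. These are illustrations, because the article gives no survival distribution, and the survival that matters is that of screen-detected fatal cases.

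The size of the shift in the odds ratio cannot be derived from the article. The documents do not support a conclusion that the CC1 main result is biased by this rule: the primary odds ratio uses the unextended date and is unaffected. This is a cheap improvement to a secondary analysis.

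**What to change.** In the exposure opportunity bias section, state two things:
1. For CC1, the control's extended date is the earlier of (a) the case's date of first diagnosis plus the assumed lead time and (b) the case's date of death.
2. Only controls matched to a screen-detected case are extended.

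Dates of death and diagnosis, tumour detection mode and screen dates are already listed in Table 1, so no new data are needed. The cost is a sentence of text, a simple date cap in the code, and a sensitivity result slightly less favourable to screening.

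Controls D should not be re-screened for being alive and disease-free at the extended date. That would select controls on events after the index date and introduce a selection problem that the present rule does not have.
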